## Abstract

**Background:**

Placental dysfunction underlies major obstetric complications, including preeclampsia, fetal growth restriction, preterm birth, and stillbirth. While early identification of pregnancies at high risk of complications enables preventive interventions, current screening methods based on traditional risk factors have limited accuracy.

**Objective:**

This study aims to develop robust prediction models for placental dysfunction–related pregnancy disorders across 3 gestational windows and to determine the optimal delivery time by integrating maternal characteristics, biophysical measurements, and maternal circulating biomarkers.

**Methods:**

The Placental Health Study is a prospective cohort study conducted at the Maternal Fetal Medicine Unit at Gold Coast University Hospital, Australia. Singleton pregnancies are enrolled at 11 to 13 weeks, 26 to 28 weeks, and 35 to 36 weeks of gestation and are followed until delivery. Exclusion criteria are multiple pregnancies, major fetal anomalies, maternal age below 18 years, and inability to provide informed consent. Clinical data, standardized ultrasound and Doppler measurements, hemodynamic parameters, and biospecimens (serum, plasma, whole blood RNA, and urine) are collected at each visit. Three gestational age-specific datasets (11‐13 weeks, 26‐28 weeks, and 35‐36 weeks) will be constructed for model development. Prediction models will be developed using multivariable logistic regression. Competing risks (Fine and Gray) models will be used as sensitivity analyses for outcomes related to gestational age at delivery. Bayesian updating will be applied to refine existing Fetal Medicine Foundation risk estimates using additional biomarkers or variables collected later in pregnancy. Developed models will undergo internal validation via 5-fold cross-validation, with performance assessed through model discrimination, calibration, and comparison against existing approaches. Collected biospecimens will also be analyzed for angiogenic markers and exploratory omics studies.

**Results:**

Recruitment occurred from June 2022 to February 2026, enrolling 1267 participants. As of submission, 1072 (84.6%) participants have completed their pregnancies, 144 (11.4%) participants remain active in follow-up, and 51 (4%) were withdrawn or had missing or duplicated data. Clinical data have undergone preliminary cleaning and descriptive analysis. Biospecimens are being processed for biomarker quantification and exploratory molecular analyses. Two to three publications are anticipated in late 2026 or early 2027.

**Conclusions:**

This cohort establishes a comprehensive database and biospecimen repository to advance prediction of placental dysfunction–related complications. Three-stage recruitment integrated into routine clinical care enhances feasibility and translation potential, enabling dynamic risk assessment and investigation of temporal biomarker changes. Although the single-center design may limit generalizability, warranting future external validation, the interdisciplinary research team brings diverse expertise that strengthens study depth and scope.

## Introduction

Placental dysfunction represents a critical pathogenic mechanism underlying pregnancy complications, including preeclampsia, fetal growth restriction (FGR), preterm birth, and stillbirth [1,2]. These disorders collectively affect around 10% of pregnancies worldwide, significantly contributing to maternal and perinatal mortality and morbidity [3-6]. They impose a substantial health care burden through increased surveillance requirements, emergency cesarean deliveries, and neonatal intensive care [7-9], and also increase long-term cardiovascular and metabolic disease risks for both mothers and offspring [10,11].

Preeclampsia and FGR frequently coexist with evidence of impaired placentation and placental function, increasing the risks of preterm birth and stillbirth [12,13]. Research has shown that these complications share common pathogenic pathways characterized by complex maternal-fetal-placental interactions [2,3,14]. Placental dysfunction acts as the primary pathophysiological driver, originating from impaired trophoblast invasion and uteroplacental spiral artery remodeling during early pregnancy, resulting in reduced placental perfusion and insufficiency [1,15,16].

Early risk identification of high-risk pregnancies enables targeted preventive interventions and reduces unnecessary intensive care for low-risk cases. Traditional screening methods based on maternal risk factors lack precision, but recent advances in biophysical and biochemical assessments have improved early risk assessment accuracy [17]. Doppler ultrasound measurements from maternal uterine and ophthalmic arteries can provide valuable insights into endothelial health and placental insufficiency [13,18,19]. Additionally, maternal serum angiogenic factors, specifically soluble fms-like tyrosine kinase-1 (sFlt-1) and placental growth factor (PlGF) have emerged as robust biomarkers for screening and diagnosing preeclampsia and other placenta-related complications [20,21].

The first-trimester prediction model developed by the Fetal Medicine Foundation (FMF), integrating maternal factors, mean arterial pressure (MAP), uterine artery pulsatility index (UtAPI), and PlGF, identifies approximately 90% of early preeclampsia (requiring delivery <32 weeks), 75% of preterm preeclampsia (delivery <37 weeks), and 41% of term preeclampsia cases at a 10% screen-positive rate [22]. This approach also detects 56% of early small for gestational age (SGA; delivery <32 weeks) and 46% of preterm SGA (delivery <37 weeks) neonates [23]. Clinical trials have demonstrated that prophylactic aspirin (>100 mg) combined with the first-trimester prediction model effectively prevents preterm preeclampsia and its associated adverse outcomes [24].

Despite these advances, predicting and preventing late-onset or term preeclampsia and FGR remains challenging due to their heterogeneous pathophysiology. These conditions exhibit less pronounced angiogenic biomarker alterations and weaker associations with placental dysfunction than early-onset cases [25]. Although causing fewer adverse outcomes, term complications have a higher prevalence, thus constituting a substantial health care burden [26]. Furthermore, low-dose aspirin appears to be less effective in preventing term preeclampsia [24]. Recent research proposes that risk stratification at 35 to 36 weeks of gestation with planned birth may offer a potential preventive strategy for managing term preeclampsia [27]. However, determining optimal delivery timing based on individualized risk stratification requires more investigation. Emerging evidence links maternal cardiovascular maladaptation and altered hemodynamic profiles with preeclampsia and FGR development, providing new directions for improving prediction models [28,29]. Current research remains limited on combining hemodynamic measurements with placental dysfunction markers to enhance prediction accuracy.

This prospective cohort study aims to develop enhanced prediction models for placental dysfunction–related complications and define optimal delivery timing. Candidate predictors will be selected a priori based on four guiding principles: (1) established inclusion in validated prediction models and current screening approaches (maternal characteristics, MAP, uterine artery Doppler, and angiogenic biomarkers used in the FMF prediction models), (2) biological plausibility and prior evidence linking placental dysfunction and maternal cardiovascular maladaptation with preeclampsia and FGR (eg, ophthalmic artery Doppler and arterial stiffness measures), (3) feasibility of implementation within routine maternity care pathways, and (4) the potential incremental predictive value of novel biomarkers derived from stored biospecimens and exploratory omics approaches. By integrating clinical factors, biophysical parameters, and maternal circulating biomarkers across 3 critical gestational windows, this study will improve risk stratification and guide clinical decision-making in perinatal care. Furthermore, the comprehensive dataset and biobank will facilitate investigation of novel biomarkers and pathophysiological mechanisms underlying placental dysfunction.

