#### Maternal Circulating Biomarker Measurements

Collected biological samples will be analyzed for maternal circulating biomarkers. Maternal serum levels of PlGF and sFlt-1 will be quantified using the KRYPTOR Compact Plus immunoanalyzer (BRAHMS Thermo Fisher Scientific), followed by calculation of the sFlt-1:PlGF ratio and multiples of the expected median using previously published equations [40,41]. In addition, exploratory omics analyses of maternal circulating biomarkers will be conducted using a nested case-control design on a subset of participants, using techniques such as quantitative polymerase chain reaction and liquid chromatography with quadrupole time-of-flight mass spectrometry.

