#### Primary Objectives: Prediction Model Development

Multivariable logistic regression will serve as the primary analytical approach for prediction model development at 3 gestational windows (11‐13 weeks, 26‐28 weeks, and 35‐36 weeks of gestation) to address both primary objectives 1 and 2. Clinically relevant candidate predictors are predefined and entered into multivariable models, followed by model reduction to achieve parsimony (eg, backward elimination with a retention threshold of *P*<.10). Nonlinear relationships between continuous variables and the log odds of the outcomes will be tested with the inclusion of polynomial terms up to the third degree, which will be kept in the model if statistically significant.

For each patient, this method estimates a predicted probability of developing the outcome based on the log odds of the outcome. For primary objective 1, the predicted probabilities can be used to define low- and high-risk subgroups at predefined gestational age thresholds. Specifically, a risk threshold will be defined based on clinically relevant screen-positive rates (eg, 10%, 15%, or 20%) to balance sensitivity and specificity for clinical implementation. For primary objective 2, logistic regression will similarly provide predicted probabilities. In addition, Fine and Gray competing risks time-to-event models will be used as sensitivity analyses accounting for delivery without the outcome of interest (preeclampsia or FGR) as a competing event.

To further improve upon current FMF prediction models, a Bayesian updating approach will be applied to refine existing FMF first-trimester risk estimates using additional biomarkers and clinical variables collected later in pregnancy. The FMF first-trimester risk estimate will be used as the prior probability. Likelihood ratios derived from biomarker and biophysical measurements at 26 to 28 weeks and 35 to 36 weeks will be incorporated via Markov chain Monte Carlo simulations to generate updated posterior risk distributions. This enables dynamic, individualized risk reassessment as pregnancy progresses.

All models will undergo internal validation using 5-fold cross-validation with repeated iterations to obtain stable performance estimates. Model performance will be evaluated using the following metrics:

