#### Secondary Objective Analysis

For secondary objective 1, time-to-event analyses will be used to evaluate the association between predicted risk scores and adverse maternal and perinatal outcomes after diagnosis of complications. For secondary objective 2, AUC-ROC analysis, sensitivity and specificity, and predictive values will be used to assess the individual predictive performance of each biomarker candidate. For secondary objective 3, longitudinal biomarker trajectories will be compared between participants with the outcomes of interest and those without these outcomes using linear mixed-effects models with random intercepts and slopes for each participant. Exploratory proteomics and metabolomics analyses will be performed on a subset of samples to identify novel biomarkers and biological pathways associated with placental dysfunction.

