x PIV: pulsatility index for veins.

y RI: resistive index.

z EDV: end-diastolic velocity.

aa PSV: peak systolic velocity.

ab HbA_1c_: hemoglobin A_1c_.

ac OGTT: oral glucose tolerance test.

ad PPROM: preterm premature rupture of membranes.

ae FBS: fetal blood sampling.

af SCN: special care nursery.

ag NICU: neonatal intensive care unit.

ah GH: gestational hypertension.

ai GDM: gestational diabetes mellitus.

A subset of samples has undergone preliminary biomarker quantification, including measurement of angiogenic markers (sFlt-1 and PlGF), and additional omics-based analyses are underway. Interim analyses have been conducted comparing clinical variables and biomarkers between participants with and without complications. It is anticipated that 2 to 3 primary publications will be ready in late 2026 or early 2027, including evaluation of maternal circulating biomarkers and exploratory analyses of novel biomarker candidates identified through omics techniques.

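### Omics markers still to be discovered in this cohort are listed as a priori candidate predictors, and their incremental value is liable to be overstated unless discovery is nested or kept separate

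*Protocol article*

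**What the plan says.** The Introduction of the protocol article states: "Candidate predictors will be selected a priori based on four guiding principles". The first three principles are prior inclusion in validated models, biological plausibility with prior evidence, and feasibility in routine care. The fourth is "the potential incremental predictive value of novel biomarkers derived from stored biospecimens and exploratory omics approaches".

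The section Primary Objectives: Prediction Model Development repeats the claim of prior choice: "Clinically relevant candidate predictors are predefined and entered into multivariable models". Model reduction follows, for example backward elimination. All models are then internally validated by repeated 5-fold cross-validation.

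The section Maternal Circulating Biomarker Measurements says that "exploratory omics analyses of maternal circulating biomarkers will be conducted using a nested case-control design on a subset of participants". Secondary Objective Analysis gives the purpose: proteomics and metabolomics "will be performed on a subset of samples to identify novel biomarkers and biological pathways associated with placental dysfunction". Results reports that further omics work was in progress at submission. The Discussion mentions adding novel candidates to existing prediction models, and leaves external validation to a later phase.

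**The concern.** A predictor is a priori when the reason for considering it comes from outside the data used to fit and judge the model. A marker picked because it separates this cohort's cases from its controls does not meet that test for models built in this cohort.

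The risk is optimism from selection. If the markers are chosen once on the outcome, and only the fitted model is then cross-validated in the same women, each held-out fold has already helped to choose the markers. Cross-validation then removes the optimism of estimating coefficients, but not that of choosing the markers. A noise marker can appear to improve prediction, and a gain over the established first-trimester model could be reported that would not recur elsewhere.

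**Working it through.** **1. Passages side by side.** The Introduction and the model-development section describe candidates fixed beforehand. The biomarker section, the secondary analysis and Results describe omics markers still being sought by outcome comparison in part of this cohort. Principle 4 makes the second group a route into the first. Both descriptions cannot hold for the same markers.

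**2. The plan's own figure.** Sample Size Estimation gives about 1700 participants for 10% incidence, at most 15 predictors and a target AUC of 0.75. An AUC of 0.75 at 10% prevalence corresponds to a Cox-Snell R² of 0.0747 (binormal simulation). The shrinkage criterion is n = P / [(S − 1) ln(1 − R²/S)]. With P = 15 and an assumed S = 0.90:

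- R²/S = 0.0747/0.90 = 0.0830, and ln(1 − 0.0830) = −0.0867
- n = 15 / (0.10 × 0.0867), about 1731 before rounding of the inputs

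This is within 2% of 1700, so the figure reproduces. It allows for 15 candidates. Markers screened in an omics step are not among them.

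**3. Size of the possible bias.** Inputs from the article:

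- N = 1072 completed + 144 ongoing = 1216
- 10% events, so 122 cases
- one base predictor with AUC 0.75, that is, a mean shift of √2 × z(0.75)

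Assumptions, because the article does not give these sizes:

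- discovery sets of 50 + 50 or 100 + 100
- 100, 500 or 1000 independent noise markers, with a true incremental value of zero
- the three markers with the largest absolute case-control t statistic added to a logistic model
- 5-fold cross-validation, 60 repetitions per setting

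Mean cross-validated AUC:

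| Discovery set | Markers | Discovery women: base | Chosen once | Gain | Chosen in each fold | Full cohort: base | Chosen once | Gain |
|---|---|---|---|---|---|---|---|---|
| 50+50 | 100 | 0.751 | 0.801 | +0.050 | 0.680 | 0.749 | 0.748 | −0.001 |
| 50+50 | 500 | 0.755 | 0.832 | +0.077 | 0.659 | 0.753 | 0.753 | 0.000 |
| 50+50 | 1000 | 0.744 | 0.831 | +0.087 | 0.643 | 0.745 | 0.746 | +0.001 |
| 100+100 | 100 | 0.747 | 0.770 | +0.023 | 0.698 | 0.751 | 0.755 | +0.004 |
| 100+100 | 500 | 0.752 | 0.793 | +0.041 | 0.694 | 0.752 | 0.760 | +0.008 |
| 100+100 | 1000 | 0.756 | 0.803 | +0.047 | 0.696 | 0.752 | 0.759 | +0.007 |

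Judged in the discovery women, noise gains about +0.02 to +0.09. When selection is repeated inside each fold, the gain vanishes and the AUC falls below the base, as it should for noise. Judged in the full cohort, the false gain is about 0.00 to +0.01.

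**4. Which case applies.** The full-cohort columns require every woman to have the marker measured. The article plans omics only on a subset, so as written the data needed for the near-nil case would not exist.

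**The case against.** The strongest reply is that omics is kept apart from the primary models. It is labelled exploratory wherever an analysis is planned, it sits under secondary objective 3, and Table 1 lists no omics marker among the biochemical measurements. The Discussion remark is an aspiration and not an analysis step. Whether selection is repeated within folds is a detail that a fuller protocol or SAP may settle.

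Much of this stands. A reader might infer that omics markers will certainly be tested in the women who selected them and that their value will be overstated. The documents do not say so, and they do not say that cross-validation begins only after selection. The bias is conditional.

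Two other tempting readings also fail:

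- **Predictive values.** The plan that "predictive values will be used to assess the individual predictive performance of each biomarker candidate" might be taken to mean predictive values computed in a case-enriched subset. That sentence belongs to secondary objective 2, which the Secondary Objectives section restricts to clinically tested biomarkers. The case-control sampling is stated only for the omics work.
- **Interim comparisons.** Results says: "Interim analyses have been conducted comparing clinical variables and biomarkers between participants with and without complications". This might suggest that predictors were picked from those results. Such comparisons match the planned Descriptive Statistics, and nothing says that they chose predictors.

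What the reply does not answer is the wording of the selection rule. The Introduction names omics-derived markers as a route to a priori candidacy, and the rest of the article shows that they cannot be a priori. That is a contradiction in the text, not a detail left for later.

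**Conclusion.** The contradiction holds without any assumption: markers yet to be found by case-control comparison in this cohort are data-driven. The consequence is conditional. Their incremental value is liable to be overstated unless discovery is repeated inside the cross-validation or the markers are tested in women outside the discovery subset.

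The size depends on choices that the article does not state: a false AUC gain of about +0.02 to +0.09 if judged in the discovery women, and about 0.00 to +0.01 if the markers were assayed and judged across the full cohort. These figures rest on the assumed subset sizes, marker counts, three selected markers, independent noise and a base AUC of 0.75. They show what could happen and do not forecast this study's result. Omics on a subset only, with external validation deferred, leaves the risk real enough to deserve a change of method as well as of wording.

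**What to change.** 1. Limit the a priori candidate list for the primary models to principles 1 to 3, and lock that list before the models are fitted.
2. Remove principle 4 as a route into the primary models. Describe any model with added omics markers as exploratory.
3. State that any claim of incremental value for such markers will rest on one of three bases: discovery repeated within each cross-validation fold, evaluation in cohort members outside the discovery subset, or the planned external validation.

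The cost is mainly wording and programming. Evaluation outside the subset would also mean assaying stored samples from further women. The downside is that novel markers could not be claimed as validated additions on the strength of the discovery subset alone.

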## Methods

### Study Design

The Placental Health Study is a single-center, prospective cohort study conducted at the Maternal Fetal Medicine (MFM) Unit, Gold Coast University Hospital (GCUH), Queensland, Australia, and commenced in June 2022. Figure 1 provides an overview of the study design and data collection procedures.

**Figure 1. F1:**
[figure not shown]
Overview of study design and data collection.

### Study Objectives

#### Primary Objectives

The primary objectives of this study are as follows:

To improve current predictive models or develop new predictive models for placental dysfunction–related pregnancy complications, including preterm preeclampsia and FGR, at 2 critical gestational periods: the first trimester (11‐13 weeks) and the second trimester (26‐28 weeks)To establish third-trimester (35‐36 weeks) models to predict term preeclampsia and FGR and to define the optimal time for delivery.

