## Discussion

This protocol describes a prospective cohort study aimed at developing advanced prediction models for placental dysfunction–related pregnancy complications, allowing for dynamic and personalized accurate risk assessment throughout the pregnancy. First- and second-trimester prediction models aim to enhance early risk assessment for placental dysfunction–related complications (preeclampsia, FGR, preterm birth, and stillbirth), and the third-trimester model focuses on predicting the onset of term complications (preeclampsia and FGR) and determining optimal delivery timing. This comprehensive strategy advances personalized obstetric care through evidence-based risk stratification.

The FMF first-trimester prediction model shows superior performance compared with traditional risk-factor–based checklists [17]. By combining maternal factors with measurements of MAP, UtAPI, and serum PlGF, this model is the most effective method for predicting early-onset and preterm preeclampsia, achieving detection rates of 90% and 75%, respectively [22,43]. This model has been validated across diverse populations, consistently demonstrating predictive performance comparable to the original studies and has been tested in randomized clinical trials [24,44-48]. Importantly, when coupled with prophylactic low-dose aspirin administration starting before 16 weeks’ gestation in high-risk pregnancies, this screening strategy reduces preterm preeclampsia by more than 60% [24,49]. In addition, the model achieves detection rates of 56% for early SGA fetuses (<32 weeks) and 46% for preterm SGA neonates (<10th percentile), with aspirin use potentially reducing the incidence of preterm SGA by 20% and early SGA by 40% [23].

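### The delivery-timing half of primary objective 2 is not answered by the risk models assigned to it

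*Protocol article*

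**What the plan says.** Under Primary Objectives, the second objective has two parts: third-trimester models for term preeclampsia and FGR, and "to define the optimal time for delivery". The Abstract's Objective repeats the timing aim. The end of the Introduction says the study aims to "develop enhanced prediction models for placental dysfunction–related complications and define optimal delivery timing", and the opening of the Discussion describes the third-trimester model as "determining optimal delivery timing".

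Study Design describes a "single-center, prospective cohort study", so delivery time is observed and not assigned.

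Under Primary Objectives: Prediction Model Development, "Multivariable logistic regression will serve as the primary analytical approach for prediction model development" at the three gestational windows, "to address both primary objectives 1 and 2". On the second objective it then says: "For primary objective 2, logistic regression will similarly provide predicted probabilities". Fine and Gray models are added as sensitivity analyses "accounting for delivery without the outcome of interest (preeclampsia or FGR) as a competing event".

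**The concern.** A claim about the best time to deliver needs a contrast: what is expected, for mother and baby, if delivery takes place in a given week, against what is expected if the pregnancy continues. It also needs a stated criterion for calling one option better. The methods name an analysis for this objective and say that it covers the objective, but that analysis returns a risk of disease. If a statement on delivery time were later drawn from those risks, readers could take it as the result of a primary analysis and act on it, although nothing in the plan had tested it.

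**Working it through.** **1. What each planned analysis estimates, set against what timing requires**

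| Planned analysis (article section) | What it gives | Contrast between delivery weeks? |
|---|---|---|
| Logistic regression (Prediction Model Development) | Probability of the outcome under the delivery practice that occurred | No |
| Fine and Gray sensitivity analysis (same section) | Cumulative incidence by gestational time, delivery without disease as competing event | No: delivery is a competing event, not a strategy under comparison |
| Bayesian updating (same section) | First-trimester risk revised with later measurements | No |
| Performance metrics (same section) | Discrimination, calibration, screening accuracy, comparison with guideline scores | No |
| Secondary objective 1 (Secondary Objective Analysis) | Association of risk score with adverse outcomes after diagnosis | No: not arranged by week of delivery |
| Secondary objectives 2 and 3 (same section) | Single-biomarker accuracy; biomarker trajectories | No |

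No row defines a criterion for the best time, and none relates neonatal outcomes to week of delivery.

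**2. Why predicted risk cannot stand in for timing**

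Under Definitions of Preeclampsia and FGR, term preeclampsia requires delivery at 37 weeks or later. A woman delivered before disease appears is a non-case. The modelled risk therefore already depends on when women were delivered. It is not the risk that would apply under a different delivery time.

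**3. What the sample size was built for**

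Inputs from Sample Size Estimation: incidence 10%, up to 15 predictors, target AUC 0.75, stated result about 1700. Assumption: a shrinkage target S of 0.9, which the article does not give. Simulation with a normally distributed linear predictor converts AUC 0.75 at 10% incidence to a Cox-Snell R² of 0.0748.

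n = P / [(S − 1) × ln(1 − R²/S)] = 15 / [(−0.1) × ln(1 − 0.0748/0.9)] = 15 / (0.1 × 0.0868) ≈ 1728

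This agrees with the stated figure to within 2%. Its inputs are those of a prediction model; no delivery-timing contrast enters.

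**4. What data exist for a narrower question**

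Table 1 lists gestational age at delivery, onset of labor, gestational age at diagnosis, and neonatal outcomes (Apgar scores, cord gases, special care or intensive care admission). Week-specific risk in ongoing pregnancies can therefore be estimated. Its precision will be limited. From Results, 1267 − 51 = 1216 participants; at the article's assumed 10% prevalence, 0.10 × 1216 ≈ 122 cases over all disorders and gestations. Term cases among women seen at 35 to 36 weeks, split by week, would be fewer.

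**5. Fine and Gray and the risk in an ongoing pregnancy (illustration only)**

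Subdistribution hazard / cause-specific hazard = (1 − F1 − F2) / (1 − F1), where F1 is the cumulative incidence of disease and F2 the share delivered without disease. The values below are assumed; the documents give none by week.

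| F2 | F1 near 0: ratio (inverse) | F1 = 10%: ratio (inverse) |
|---|---|---|
| 20% | 0.80 (1.25) | 0.70/0.90 = 0.78 (1.29) |
| 50% | 0.50 (2) | 0.40/0.90 = 0.44 (2.25) |
| 80% | 0.20 (5) | 0.10/0.90 = 0.11 (9) |

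The table shows only that the two hazards differ, and differ more as deliveries accumulate. It measures no error in the plan, because the article does not propose to read the subdistribution hazard as the weekly risk of a continuing pregnancy.

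**The case against.** The strongest reply is that a journal article condenses, and that the step from risk to timing may sit in a fuller document. The Introduction and Discussion describe a route in which risk stratification at 35 to 36 weeks feeds planned birth. Later in the Discussion the cohort is said only to facilitate the development of timing strategies, and use of the framework is made conditional on validation. This softer wording stands where it occurs. It does not remove the mismatch, because the methods section names the analysis for objective 2 and says that it covers that objective.

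A reader might go further than the documents allow in four ways.

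- *That objective 2 as a whole cannot be answered.* The prediction half can be, by the models named. The timing half is unanswered by the planned analyses, not by the data: the variables in Table 1 would allow a timing comparison to be specified.
- *That clinicians chose the delivery week from the same risk markers.* No section says how delivery was decided. For sFlt-1 and PlGF the text points the other way: Maternal Circulating Biomarker Measurements puts quantification in the future, and Results reports it for only a subset of samples. Confounding by indication through blood pressure, growth or Doppler findings is plausible, but it is an assumption.
- *That Fine and Gray is the wrong model.* For cumulative incidence under current practice it is a legitimate sensitivity analysis, and it gives risk over gestational time, so the plan is not confined to a single probability per woman.
- *That the fold differences above are the size of an error.* They rest on assumed shares and change with the assumed incidence.

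**Conclusion.** The point holds for the delivery-timing clause of primary objective 2 and its repetitions in the Abstract, Introduction and opening of the Discussion. The analyses assigned to it yield risk of term preeclampsia or FGR under observed delivery practice. Nothing planned turns that risk into a comparison of delivery times. This is a stated mismatch between objective and method, not an omitted detail.

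Its extent is one of the two parts of one of the two primary objectives. The conclusion comes from reading the sections together and depends on no calculation. The prediction models, data collection and sample size basis are untouched. That delivery week is confounded by indication remains an assumption, although a reasonable one in an observational cohort.

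**What to change.** 1. In the Abstract's Objective, the end of the Introduction, Primary Objectives and the opening of the Discussion, replace the timing clause with: to estimate gestational-week-specific risk of term preeclampsia and FGR in ongoing pregnancies, to inform later research on delivery timing.
2. Support this with a weekly cause-specific model from the 35 to 36 week visit. The risk set is women undelivered and undiagnosed; delivery without disease is censoring. State the assumption that censoring is independent given the covariates, and include the measured markers that could plausibly influence delivery.
3. Report it with neonatal outcomes by week of delivery, from data already collected.
4. Keep Fine and Gray for cumulative incidence under current practice.
5. Label any comparison of delivery weeks exploratory, state the outcome criterion, and adjust for confounders.

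The weekly model contains no contrast between delivery weeks. It supports the narrowed objective and does not by itself define a best time. If the sponsor wishes to keep the timing claim, a separate comparison of delivery-time strategies, with a defined outcome criterion and control of time-varying confounding, must be specified; precision for that has not been planned.

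The cost is a change of wording and one further model on existing data, feasible before the publications expected in late 2026 or early 2027. The downside is a weaker headline claim and imprecise weekly estimates.
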